## Abstract

**Background:**

A high perioperative inspiratory oxygen fraction may reduce the risk of surgical site infections, as bacterial eradication by neutrophils depends on wound oxygen tension. Two trials have shown that a high perioperative inspiratory oxygen fraction (FiO_2 _= 0.80) significantly reduced risk of surgical site infections after elective colorectal surgery, but a third trial was stopped early because the frequency of surgical site infections was more than doubled in the group receiving FiO_2 _= 0.80. It has not been settled if a high inspiratory oxygen fraction increases the risk of pulmonary complications, such as atelectasis, pneumonia and respiratory failure. The aim of our trial is to assess the potential benefits and harms of a high perioperative oxygen fraction in patients undergoing abdominal surgery.

**Methods and design:**

The PROXI-Trial is a randomized, patient- and assessor blinded trial of perioperative supplemental oxygen in 1400 patients undergoing acute or elective laparotomy in 14 Danish hospitals. Patients are randomized to receive either 80% oxygen (FiO_2 _= 0.80) or 30% oxygen (FiO_2 _= 0.30) during surgery and for the first 2 postoperative hours. The primary outcome is surgical site infection within 14 days. The secondary outcomes are: atelectasis, pneumonia, respiratory failure, re-operation, mortality, duration of postoperative hospitalization, and admission to intensive care unit. The sample size allows detection of a 33% relative risk reduction in the primary outcome with 80% power.

**Discussion:**

This trial assesses benefits and harms of a high inspiratory oxygen fraction, and the trial may be generalizable to a general surgical population undergoing laparotomy.

**Trial registration:**

ClinicalTrials.gov identifier: NCT00364741.

## Background

Surgical site infection is a common and serious complication after abdominal surgery [1]. It is essential to optimize perioperative conditions because the first hours following bacterial contamination are critical for establishing the wound infection [2]. Wound oxygen tension is often low at the end of surgery and this is unfortunate, because bacterial eradication depends on this factor *via *oxidative killing by neutrophils [3-6]. The incidence of surgical site infections may therefore be reduced by increasing the perioperative arterial oxygen tension through increased inspiratory oxygen fraction.

Before we initiated our multicenter trial "PeRioperative OXygen Fraction – effect on surgical site Infection and pulmonary complications after abdominal surgery" (PROXI), we undertook a meta-analysis on trials comparing the effect of perioperative inhaled oxygen fraction of 0.80 with 0.30 on the frequency of surgical site infection. This was performed using the trial sequential analysis method [7-9] and in accordance with international recommendations [10,11].

When searching MEDLINE, Cochrane Central Register of Controlled Trials, and EMBASE (search terms, see Appendix) four clinical trials including 1003 patients were found [12-15].

In a random-effects model, the overall pooled effect of an inspiratory oxygen fraction of 0.80 was a reduction of the occurrence of surgical site infections. The relative risk reduction was 19% [95% CI: -68% to 61%], P = 0.57, but a large heterogeneity, I^2 ^= 74%, was also found (Fig. 1). This may primarily be explained by the findings in one trial [15], in which the high oxygen fraction was associated with an increase in the frequency of surgical site infection of 122% [95% CI: 8% to 458%]. In that trial, however, mixtures of oxygen and nitrous oxide were given, the surgical site infections were assessed retrospectively by chart review, and the allocation was not fully concealed.

**Figure 1 F1:**
[figure not shown]
Meta-analysis comparing perioperative inspiratory oxygen fractions of 0.80 and 0.30/0.35 on surgical site infection.

When inspired in a high concentration, oxygen may result in pulmonary complications, but although 1003 patients have participated in the previous trials [12-15], this important question has been studied only in 30 patients [16]. This subgroup of patients from the first trial of supplemental oxygen [13] underwent pulmonary function test together with chest radiographs and computed tomography (CT) scans on the day after surgery. A high oxygen fraction was not found to be associated with significant changes in any test, but CT-determined atelectasis tended to be more common in patients receiving 80% oxygen (94% vs. 64%, P = 0.12). Preoxygenation with 100% oxygen for 5 minutes has also been associated with increased risk of atelectasis formation when compared to 60% [17]. A high oxygen fraction has also been related to harms such as an increased risk of airway inflammation [18], poor regulation of blood glucose [19], changes in the cardiac index [20], and to benefits such as improved healing of colorectal anastomosis [21] and reduced frequency of postoperative nausea and vomiting [22,23].

We designed the PROXI-Trial to assess the potential benefits and harms of a high perioperative oxygen fraction in patients undergoing laparotomy, the primary end point being surgical site infection.

## Methods and design

### Trial design

The PROXI-Trial is an ongoing, randomized, parallel group, multicenter, patient- and assessor blinded trial, launched on October 9, 2006. The trial is investigator initiated and controlled. The primary aim is to assess the effect of a high perioperative oxygen fraction on the frequency of surgical site infection in patients undergoing laparotomy. The secondary outcome measures are: atelectasis, pneumonia, respiratory failure, re-operation, mortality, duration of postoperative hospitalization, and admission to intensive care unit. Fourteen anaesthesia and surgical centres as well as one trial unit in Denmark participate in the trial.

### Inclusion criteria

Patients, aged 18 years or older, scheduled for acute or elective laparotomy are eligible for inclusion. When the laparotomy is indicated for a gynaecological disease, only patients with suspected malignancy (defined as risk of ovarian malignancy index >200 [24] or a specimen showing atypical or neoplastic cells) are included.

### Exclusion criteria

The exclusion criteria are: Surgery performed under general anaesthesia within 30 days, chemotherapy for malignancy within 3 months, inability to give informed consent, and preoperative arterial haemoglobin oxygen saturation below 90% assessed by pulse oximetry without supplemental oxygen.

### Randomization

The patients are randomized 1:1 by a central interactive voice-response system at the Copenhagen Trial Unit to ensure adequate allocation concealment. A computer generated randomization sequence with variable block size is used with the following stratification variables: Centre, diabetes mellitus, acute or elective surgery, and body mass index (<30 or ≥30 kg/m^2^).

### Intervention

After induction of anaesthesia and tracheal intubation, patients randomized into the supplemental oxygen group are given an inspiratory oxygen fraction (FiO_2_) of 0.80 until end of surgery. Patients are administered a FiO_2 _of 0.80 during the first two hours following extubation by means of a non-rebreathing face mask with a reservoir (High Concentration Oxygen Mask, Intersurgical Ltd, Wokingham, UK) with a flow of 14 litres of oxygen and 2 litres of air per minute. This mixture of oxygen and air contains a slightly higher oxygen fraction (0.901), because even the manufacturer's test resulted in only 85% delivered oxygen in a situation with masks fully sealed to a flat surface and 15 litres of oxygen per minute (Intersurgical Test Report, April 2008). With an estimated flow of ambient air into the mask of approximately 3.0 litres per minute, we estimate that the chosen mask and mixture delivers a FiO_2 _close to 0.80. This was confirmed in a test before the trial was initiated.

The patients randomized into the control group are given a FiO_2 _of 0.30 after tracheal intubation and until extubation, after which they receive a flow of 2 litres of oxygen and 14 litres of air per minute through a non-rebreathing facemask with reservoir (High Concentration Oxygen Mask, Intersurgical Ltd, Wokingham, UK).

In both groups, it is allowed to increase FiO_2 _if hypoxia is detected or suspected in order to keep the arterial oxygen saturation above 94% and the arterial oxygen tension above 9 kPa. Positive end expiratory pressure (PEEP) is used at a level chosen by the attending anaesthetist. At the end of the intervention period, oxygen is administrated only at the physician's discretion and according to usual clinical practice.

### Blinding

Cardboard shields are placed on the side of the anaesthesia machines to keep the surgical team blinded to group allocation. In the post anaesthesia care unit, opaque bags cover the flow meters. Information about perioperative FiO_2_, arterial oxygen partial pressure (PaO_2_) as well as flow of oxygen and air is collected on a separate paper form, placed in a sealed opaque envelope when patients are discharged from the post anaesthesia care unit. Any urgency requiring opening of the envelope will be reported. The patients are not informed of their group allocation during the trial or follow-up.

Patients are asked after follow-up which group they believe they were allocated to in order to evaluate patient blinding and the possible related bias in the reporting of adverse events. If patients answer supplemental oxygen or control group, they are asked to indicate why.

The Steering Committee is also blinded and has no access to patient allocation during the trial. An independent statistician will analyze the PROXI data under code (treatment A and B) and prepare a blinded version of the results. All sections of the manuscript, including the discussion and conclusion, will be written in two versions; one assuming treatment A is supplemental oxygen and treatment B is control treatment, and another manuscript based on the reverse assumption [25]. All authors must approve both versions before demasking the allocation groups.

### Standard treatment

After preoxygenation, anaesthesia is induced with propofol or thiopental supplemented with remifentanil, fentanyl, sufentanil, or alfentanil and maintained with propofol, sevoflurane, or desflurane. The use of nitrous oxide is not allowed. Tracheal intubation is facilitated with succinylcholine or an intermediate acting non-depolarizing neuromuscular blocking agent. Both groups are given a FiO_2 _of 1.0 until tracheal intubation and again immediately before extubation. The patients are ventilated to assure normocapnia (defined as an arterial carbon dioxide tension of 4.5 to 6.0 kPa if arterial blood sampling is carried out, otherwise capnography is used to adjust ventilation).

Several important elements of the perioperative care [26-30] are stressed in the trial protocol (Table 1). The protocol recommends cefuroxime 1.5 g and metronidazole 1.0 g given intravenously as standard antibiotic choice, but we define appropriate antibiotic therapy according to Table 2[31] because of the high number of surgical procedures. Antibiotic therapy must be given within 60 minutes of skin incision, and we consider 'timely administration' to be fulfilled if the first and second antibiotic is given before skin incision.

**Table 1 T1:** Trial protocol for perioperative care of patients undergoing laparotomy.

Protocol element	Description
Preoperative:	
Bowel preparation	No routine oral preparation used for colonic resection.*
Fasting guideline	Allowed to drink clear fluids 2 hours before anaesthesia.*
Perioperative:	
Epidural analgesia	Placed at thoracic level corresponding to the incision in elective procedures and used intraoperatively.*
Fluid therapy	A preoperative deficit in acute surgery corrected preoperatively, but no routine fluid preload used. Fluid given only to replace measured or calculated deficits (no third space loss) aiming at a body weight increase less than 1 kg. Peroperative blood loss replaced 1:1 with colloids, not exceeding 500 mL more than estimated blood loss. Blood transfusion initiated if blood loss exceeds 20 mL/kg, considering the patient's haematocrit. Vasopressors or reduction of epidural infusion if hypotension.^¤^
Temperature control	Warmed fluids if large infusions and upper body air-warming device used. Core temperature measured continuously, aiming at 36 to 37°C.*
Glucose control	Aim: Blood concentration between 5 and 11 mmol/L.
Surgical technique	Shortest possible abdominal incision. No intraabdominal drain, no nasogastric tube unless essential for intraoperative gastric decompression, postoperative ileus prophylaxis or postoperative nutrition.*
Neuromuscular function	Monitored with a nerve stimulator; patients are not extubated before train-of-four ratio is above 0.90.^#^
Postoperative:	
Pain relief	Epidural analgesia continued for 2 days postoperatively. Paracetamol 4 g daily and a non-steroidal anti-inflammatory drug before discontinuing the epidural analgesia. An opioid is given intravenously if pain score at rest is above 3 on visual analogue scale (0–10).*
Fluid therapy	Oral intake as early as possible, blood loss replaced 1:1 with colloids or blood transfusion according to normal clinical practice. Other deficits replaced with crystalloids in order to keep urine output above 1 mL/kg/hr.^¤^

* Fearon et al. [26]; ^# ^Berg et al. [27]; ^¤ ^Arkilic et al., Kabon et al., Brandstrup et al. [28-30].

**Table 2 T2:** Adequate perioperative intravenous antibiotic prophylaxes.

Type of surgery	Adequate perioperative antibiotic prophylaxis
Elective colorectal surgery	B or C
Elective gynaecological surgery	
Clean procedures	A
Clean-contaminated, contaminated or dirty infected procedures	B or C
Elective removal of gall bladder	None
Acute appendectomy, no perforation	None
Acute appendectomy, with perforation	B or C
Other acute laparotomy,	
Clean procedures	None
Clean-contaminated, contaminated or dirty infected procedures	B or C

A = cefuroxime 1.5 g; B = cefuroxime 1.5 g and metronidazole 1.0 g; C = ampicillin 2 g or benzylpenicillin 2 million IU in combination with gentamicin 0.240 g and metronidazole 1.0 g.

Adequate antibiotic prophylaxes divided by surgical procedure are based on the advisory statement from the National Surgical Infection Prevention Project [31].

### Baseline data

After inclusion we record demographic characteristics and data on significant comorbidity with emphasis on the following factors: Current smoking, ethanol consumption above 48 g daily, diabetes mellitus, concurrent infection, or immunosuppressive disease, chronic obstructive pulmonary disease (COPD) and other pulmonary diseases. The risk of infection is evaluated with the National Nosocomial Infections Surveillance System (NNISS) and the Study on the Efficacy of Nosocomial Infection Control (SENIC) scores [32,33].

### Perioperative data collection

Preoperative haemoglobin and peroperative change in blood glucose are measured. We record duration of anaesthesia, duration of surgery, placement of epidural catheter, type of anaesthesia, body core temperature at the end of surgery, and use of antibiotics, vasopressors, and dexamethasone. We record peroperative blood loss and the administered volume of crystalloids, colloids, and blood. Pre- and postoperative body weight is also measured, if possible.

### Follow-up

All patients must be seen daily in the postoperative period by a surgical investigator blinded to the allocated intervention. A follow-up visit is scheduled between the 13^th ^and the 30^th ^postoperative day as appropriate. The primary and secondary outcome measures are evaluated at each visit and additional information about wound characteristics in the postoperative period is collected to calculate the ASEPSIS score (Additional treatment, Serous exudate, Erythema, Purulent exudate, Separation of deep tissues, Isolation of bacteria and duration of inpatient Stay) [34]. This score (range 0–70) combines wound appearance the first 5 postoperative days with additional surgical treatment and a score higher than 20 indicates wound infection [34].

Patients presenting with symptoms of pulmonary complications are examined according to routine clinical practice by the attending physician, including chest radiographs or CT, when relevant. All chest radiographs and CT's are evaluated for infiltrate and atelectasis by the attending radiologist, who is unaware of the administered intervention.

### Outcome measures

The primary outcome is surgical site infection within 14 days, defined according to the criteria by Center of Disease Control and prevention (CDC) [35]. This definition includes superficial, deep, and organ/space infections and surgical site infection is considered present if any of these infections are diagnosed during follow-up. If a patient has a combination of superficial, deep, and organ/space infections, we report the deepest infection, except from organ/space infections that drain through the incision, which according to CDC is a deep surgical site infection [35].

The secondary outcomes are defined as follows (intervals defined as time after surgery):

• Pneumonia within 14 days, defined according to the criteria by CDC [36]. We will report the frequencies within this category of: Nosocomial pneumonia, ventilator-associated pneumonia, pneumonia due to gross aspiration, and pneumonia in immunocompromised patients [36].

• Atelectasis within 14 days is defined to be present if described in the radiologist's evaluation of chest radiograph or CT.

• Respiratory failure within 14 days, defined as need for controlled ventilation or arterial oxygen saturation below 90% despite supplemental oxygen.

• Mortality within 30 days.

• Duration of postoperative hospitalization, including readmission periods, if occurring within 30 days.

• Admission to the intensive care unit within 14 days, if not part of the postoperative care.

• Abdominal re-operation due to any reason within 14 days.

In case of uncertain outcome measures, two blinded assessors, and a third assessor in case of further disagreement, review the patient's hospital record.

### Adverse events

All recorded adverse events will be reported according to the CONSORT Statement [37]. We do not list any adverse events specifically related to supplemental oxygen in the protocol or consent form. The following adverse events are considered so frequent after surgery that they are not recorded: Pain or hypotension within the first 3 postoperative days and abnormal laboratory values that do not require medical treatment. All other adverse events are collected prospectively in the patient's case report form and specifically addressed at the follow-up visit. The reported adverse events will be categorized before the trial's allocation groups are demasked.

An adverse event is considered serious if it is fatal, life threatening, causing permanent disability or requiring prolonged hospitalization. Adverse events and serious adverse events will be reported for all randomized patients separately as frequencies for each arm. It will be reported if any adverse event results in increase or decrease of the allocated FiO_2_.

### Missing data

If patients do not meet for the follow-up visit, we contact: Hospital outpatient clinics, emergency departments, and the patient's family physician. Wound evaluation carried out in accordance with the CDC-criteria is considered adequate. In the remaining cases, the patients are interviewed by telephone, and the information obtained is used in the intention-to-treat analysis.

Missing data from daily evaluation of wound characteristics for the ASEPSIS score will be replaced by scores obtained by linear regression of score by day using the scores from the adjacent days. Missing data in patients discharged before 5^th ^postoperative day will be replaced by scores obtained by linear regression of score by day between the adjacent in-hospital score and the score at the follow-up visit [38].

Patients meeting the inclusion criteria without being randomized are prospectively recorded. Completeness of these data is established through the Danish Anaesthesia Database  and the Danish National Patient Registry [39] by searching the relevant Health Service Classification System (SKS)-codes for laparotomy procedures .

### Major protocol violations

Patients with the following major protocol deviations will not be included in the *per protocol *analysis: Not meeting the inclusion criteria, fulfilling an exclusion criterion, FiO_2 _above 0.60 for more than 1 hour in the control group, FiO_2 _below 0.60 for more than 1 hour in supplemental oxygen group, failure to use the oxygen mask more than 1 hour, no in-hospital evaluation of the outcomes for 4 consecutive days or more, no follow-up visit between 13^th ^and 30^th ^postoperative day, and unblinded outcome assessment. We considered the limit of FiO_2 _= 0.60 to represent the lowest oxygen fraction where atelectasis could not be attributed to the oxygen concentration [17].

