### Limitations

Some important limitations must be noted. Firstly, some patients in the control group may need more than the allocated 30% oxygen in order to keep arterial oxygen saturation above 94%. However, this practice is in accordance with clinical practice and we believe such pragmatic nature of the intervention is important. Our *per protocol *analysis will assess if close adherence to the protocol is associated with better outcome.

Secondly, we are not able to apply all elements of the standard treatment to all patients. Timely administration of antibiotics and epidural analgesia influences postoperative outcome, but this is not possible to achieve in all patients. The antibiotic regimen is recorded to assess whether it is adequate for the given type of surgery and the most common pathogenic bacterial flora. Protocol deviations may result in a higher frequency of surgical site infection, but that may reflect clinical practice.

Thirdly, it is possible that the mixture of different surgical procedures may be associated with the risk of overlooking a beneficial effect related to specific surgical procedures, such as colorectal resections, but the type of surgery is not always known at the time of deciding the inspiratory oxygen fraction and we are aiming at elucidating the effect of a high oxygen fraction in connection with open gastroenterological procedures in general, including emergency surgery.

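### The per-protocol set drops hypoxic patients from the control arm only, and its visit rule drops early deaths, so its result on adherence is open to selection bias

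*Protocol article*

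**What the plan says.** The section on major protocol violations lists the events that remove a patient from the per-protocol analysis. Four matter here:

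- in controls, FiO2 "above 0.60 for more than 1 hour in the control group";
- in the other arm, FiO2 "below 0.60 for more than 1 hour in supplemental oxygen group";
- "no follow-up visit between 13^th ^and 30^th ^postoperative day";
- "failure to use the oxygen mask more than 1 hour".

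The list makes no exception for oxygen raised under the protocol's own provision, for death, or for patients still intubated. The Intervention section says of both groups that "it is allowed to increase FiO_2 _if hypoxia is detected or suspected". The Limitations section accepts that "some patients in the control group may need more than the allocated 30% oxygen", and then offers the per-protocol approach as the response: that "analysis will assess if close adherence to the protocol is associated with better outcome".

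Under Outcome measures, 30-day mortality and respiratory failure are secondary outcomes. Under Statistics, intention-to-treat on all randomised patients gives the primary results.

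**The concern.** A per-protocol set supports a comparison between arms only if the patients left in each arm are still alike in prognosis. Here one exclusion is triggered by hypoxia, which arises after randomisation and plausibly marks a sicker patient, and it can act in one arm only. A control patient who needs more than 0.60 for over an hour leaves the set. The same patient allocated to 0.80 already receives that much, and any further increase breaks no rule. The remaining controls would then be healthier than the remaining 0.80 patients for reasons unrelated to oxygen.

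The visit rule raises a different problem. A patient who dies before the visit cannot attend it, so exclusion depends directly on a trial outcome.

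What is at stake is the reading of the per-protocol result. The trial sets out to assess harm as well as benefit, and a reader who takes this analysis as the answer to the adherence question would be reading a comparison tilted against 80% oxygen.

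**Working it through.** **The plan's own figures.** The article gives no frequency for any per-protocol exclusion, so there is no stated figure to reproduce on this point. The sample size does reproduce. For 16% against 10.7%, two-sided 5% and 80% power, 646 per arm are needed, or 1292 in total; 1292 / 0.90 = 1436, within 3% of the stated 1400. The 16% control rate is used below.

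**Hypoxia rule under no true effect.** Assumed, not in the article:

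- h = share of patients who would need FiO2 above 0.60 for more than 1 hour if allocated to control;
- r = their risk of the outcome relative to the other patients.

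Let b be the risk in the other patients. Both randomised arms then have risk b(1 - h + hr). Dropping the hypoxic patients from control only leaves risk b in that arm, so

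per-protocol RR (80% vs 30%) = b(1 - h + hr) / b = 1 - h + hr.

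If a fraction e of comparable patients also leaves the 0.80 arm,

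RR = [(1 - h) + (1 - e)hr] / [(1 - h) + (1 - e)h].

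For surgical site infection, with 16% in both randomised arms:

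| h | r | RR, e = 0 | control risk left, 16% / RR | RR, e = 0.5 |
|---|---|---|---|---|
| 3% | 1.5 | 1 - 0.03 + 0.045 = 1.015 | 15.8% | 0.9925 / 0.985 = 1.008 |
| 5% | 2 | 1 - 0.05 + 0.10 = 1.05 | 15.2% | 1.00 / 0.975 = 1.026 |
| 10% | 2 | 1 - 0.10 + 0.20 = 1.10 | 14.5% | 1.00 / 0.95 = 1.053 |
| 10% | 3 | 1 - 0.10 + 0.30 = 1.20 | 13.3% | 1.05 / 0.95 = 1.105 |

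At the top of the range, a true null would appear as 16% against 13.3%, a spurious difference of 2.7 percentage points. The planned difference is 16 - 10.7 = 5.3 points. For a pulmonary outcome more closely tied to hypoxia, r = 5 gives 1 - 0.03 + 0.15 = 1.12 at h = 3% and 1 - 0.10 + 0.50 = 1.40 at h = 10%.

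The direction does not depend on the values: RR exceeds 1 whenever r > 1 and e < 1. At e = 1 the shift disappears.

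**Visit rule.** No arithmetic is needed for the direction. Mortality is counted to day 30, while the set requires a visit on days 13 to 30, so every death before the visit is out. The rule is the same in both arms, so under no effect it removes equal proportions and does not move the risk ratio. It does leave any per-protocol mortality figure without early deaths. If 1-3% died before the visit (assumed), that is 1400 x 0.01 = 14 to 1400 x 0.03 = 42 patients over both arms.

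**Mask rule.** The Abstract runs the postoperative intervention over the first 2 hours after surgery; the Intervention section starts the mask period at extubation. On the former reading, a patient still ventilated at that time fails the criterion. On the latter, a patient extubated late can still meet it. The article does not settle which applies.

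**The case against.** The strongest reply is that these are exposure thresholds with a stated rationale. The 0.60 limit comes from a cited preoxygenation comparison, and each arm loses patients who received something like the other arm's exposure. A control above 0.60 for over an hour did not receive control exposure, and selection of this kind occurs in any set defined by adherence. Much of that stands: keeping such controls in would dilute the contrast, so it is a trade-off and not a correction. But the rationale explains the number; it does not make the remaining groups comparable. The rule in the 0.80 arm is not its counterpart as regards hypoxia, because low oxygen saturation leads to more oxygen, not less.

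It can also be said that the Limitations sentence claims only an association, and that a condensed article may leave the handling of deaths to the full protocol. Both are fair, and they are why the second point is put as a literal reading. Still, the sentence follows directly on the admission about controls, and a reader will take it as the answer.

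Three stronger readings are tempting and are not supported:

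- **Deaths and respiratory failures vanish from the safety results.** They do not. All outcomes are analysed by intention-to-treat, and adverse events are reported for all randomised patients. The article does not even say that the per-protocol analysis will cover mortality.
- **Patients on prolonged ventilation are necessarily dropped.** This fails for late extubation if the mask period starts at extubation.
- **All these rules remove the sickest patients from control only.** The visit and mask rules are the same in both arms.

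**Conclusion.** The point holds for the definition and interpretation of the per-protocol set. Membership depends on post-randomisation events tied to prognosis, and for hypoxia the dependence is one-sided, with a bias toward apparent harm of 80% oxygen if hypoxic patients carry higher risk.

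The size is not known. The range of about 1.02 to 1.20 for infection rests on assumed h of 3-10% and r of 1.5-3, and on no comparable patients leaving the 0.80 arm. If half of them did, the shift would roughly halve. The upper end needs both assumptions at their extremes, and the effect on infection may well be small. It could be larger for pulmonary outcomes. For mortality, the defect is loss of early deaths in both arms, not a shift in a known direction.

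The primary result is untouched, so this is a correction that should be made to a supportive analysis and does not threaten the trial's main conclusion.

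**What to change.** 1. State under Major protocol violations that a patient who died before the visit, or who had already met the outcome in question, counts as having complete follow-up for that outcome.
2. In the Limitations section, say that the exclusion-based per-protocol result is supportive and subject to selection by hypoxia. Report the exclusions by arm and by reason.
3. For the adherence question, add an analysis that keeps the randomised groups, for example a complier-average effect with randomisation as the instrument. State its assumptions, including the exclusion restriction and the threshold that defines adherence.
4. Reconcile the start of the mask period between the Abstract and the Intervention section, so that the mask criterion is unambiguous for patients not extubated at the end of surgery.

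The cost is some wording, one extra analysis on FiO2 data already being collected, and a slightly larger per-protocol set. The article describes an ongoing trial with a blinded Steering Committee, so the changes can be made before allocation is unmasked. No change to the clinical rule on raising FiO2 is proposed.
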